TNEC is a method that has been developed to rapidly induce IATH and achieve hypothermia for human CA. The technique takes advantage of the nose as a natural orifice into the head to overcome the obstacle of cooling through the skull. The upper nasal pathways provide a large diffuse surface area and vascularity that is in close proximity to the cerebral circulation. Cooling in the nasopharynx also offers the ability to cool via direct conductive mechanisms that do not rely on spontaneous circulation [22]. In the only randomized study using such approach to induce IATH [23], 200 OHCA patients were randomized during CPR, irrespective of their rhythm, to receive either TNEC or standard of care (including post-ROSC cooling at hospital). This feasibility study showed that the method was safe for pre-hospital use. Overall survival rates were similar in the two groups (15% vs. 13%). Among patients admitted to the hospital, overall survival to hospital discharge was improved, although not significantly, during IATH (44% vs. 31%, p = 0.16). In the post-hoc analysis, the sub-group of patients with time to CPR less than 10 minutes had an increased survival rate when treated by IATH (56% vs. 29%, p = 0.04). Also, TNEC increased, although not significantly (p = 0.14), the intact neurological outcome rate from 21% to 34% when compared to the control group; these beneficial effects were more pronounced in the subgroup of patients with time to CPR less than 10 minutes (43% vs. 17%, p = 0.03).

Given these supportive data, we are conducting a randomized controlled trial comparing TNEC to conventional post-ROSC cooling. The aim is to determine whether TNEC used during CPR would improve neurological outcome in patients being resuscitated from OHCA and with a time to CPR less than 15 minutes.

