### Randomization

Randomization will be carried out in blocks of four and each site will be given sets of sequentially numbered envelopes with randomization assignments provided in a 1:1 manner to distribute to the participating pre-hospital vehicles. Individual envelopes will be placed in each RhinoChill pack at the time of site initiation, and replaced as patients are enrolled. The RhinoChill pack will be carried to every potential subject, and the envelope will be opened once the subject has been qualified as meeting all inclusion and exclusion criteria. Neither EMS or hospital personnel will be blinded to treatment, since the control patients are easily distinguishable from patients undergoing device placement and nasal cooling. However, medical personnel making the final neurological assessment of the patient prior to discharge will be blinded to patient’s group assignment.

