### Statistical analysis

The primary outcome measure of this study is neurological intact survival at 90 days among all patients admitted to the hospital. Considering data from the previous trial [23], we postulated that the using of IATH with TNEC technique could improve this primary outcome from 21% to 37%. For a 80% power and α error of 0.05, the study requires 150 patients admitted to the hospital who should be randomized in each arm: however, considering a ROSC rate around 40% and 10% of lost to follow-up, the study will require a sample size of 418 patients for each arm (836 in total), regardless of initial rhythm. Analysis of data will be based on “Intention-to-treat”. A first interim analysis will be performed after 200 patients; conditional power for meeting the primary endpoint will be, if needed, recalculated at that time, and if the interim results do not correspond to the primary end-point, termination of the study for futility will be considered. In case of sample calculation exceeding 500 patients, other potential recruiting centers will be included in the study. Other interim analyses will be performed each 200 patients included. Early stopping for efficacy reasons will only be considered if major outcome differences are seen between the groups according to the Haybittle rule with a p-value ≤ 0.001.

Stratified analyses will be performed for patients whose first recorded rhythm is VF/VT versus those in whom the first recorded rhythm is PEA/asystole. Sub-group analyses will be performed for subjects where CPR was initiated within 10 minutes by a first EMS response team or where cooling was started within 15 minutes. The study is expected to last until 2016.

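### 150 admitted patients per arm give about 87% power for 21% vs 37%, not the stated 80%, and about 71% for the 21% vs 34% reported from the trial cited as the source

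*Protocol article*

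**What the plan says.** The Statistical analysis section of the protocol article gives the whole calculation in two sentences. It takes the earlier randomised trial (reference 23) as its starting point and continues: "we postulated that the using of IATH with TNEC technique could improve this primary outcome from 21% to 37" per cent. The outcome is neurologically intact survival at 90 days among admitted patients.

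The size follows: "For a 80% power and α error of 0.05, the study requires 150 patients admitted to the hospital". This number applies to each of the two arms. It is then inflated: "considering a ROSC rate around 40% and 10% of lost to follow-up, the study will require a sample size of 418 patients for each arm". Over both arms this makes 836 patients. Neither the test nor its sidedness is named. Allocation is 1:1 (Randomization section).

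The Background describes the same reference 23. It says that nasal cooling raised, without reaching significance (p = 0.14), "the intact neurological outcome rate from 21% to 34% when compared to the control group". In patients with time to CPR under 10 minutes, the figures were 43% vs 17%.

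**The concern.** Two things do not fit.

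- **Power and number.** The two rates, the alpha, the power and the number per arm are all printed, so one follows from the others. The printed number is not the one that the printed inputs produce.
- **Effect and source.** The control rate of 21% is the Background's figure for the earlier trial. The treated rate of 37% is 3 points above the Background's 34%, and no reason is given where it is introduced. The planned difference is therefore 16 points, against 13 points reported.

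What is at stake is how a non-significant result is read. The Discussion presents the trial as confirming the promising earlier results. Someone who takes 80% as the chance of detecting an effect of that size would be relying on a figure that the numbers do not support.

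**Working it through.** **Inputs.** From Statistical analysis: control rate p1 = 0.21, treated rate p2 = 0.37, alpha 0.05, power 80%, 150 per arm, ROSC about 40%, loss 10%, 418 per arm. From Randomization: 1:1 allocation. From Background: 0.21 vs 0.34 in the cited trial. Assumption: a two-sided test, because sidedness is not stated. The one-sided case is also shown.

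**1. The inflation step reproduces.** 150 / 0.40 = 375, and 375 / 0.90 = 416.7, against 418 stated. In reverse, 418 × 0.40 × 0.90 = 150.5. So 150 is the number after ROSC and loss have been allowed for.

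**2. The number per arm does not reproduce.** With d = p2 − p1 and p̄ the mean of the two rates, the pooled-variance formula is

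n = [1.960·√(2p̄(1−p̄)) + 0.842·√(p1(1−p1) + p2(1−p2))]² / d²

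For 0.21 vs 0.37, p̄ = 0.29:

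- √(2 × 0.29 × 0.71) = √0.4118 = 0.6417, and × 1.960 = 1.2577
- √(0.1659 + 0.2331) = √0.3990 = 0.6317, and × 0.842 = 0.5316
- n = (1.7893)² / 0.0256 = 125.1, so **126 per arm**
- with continuity correction, (n/4)·[1 + √(1 + 4/(n·d))]² = 137.3, so **138 per arm**

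Other choices:

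| Method (21% vs 37%, 80% power) | n per arm |
|---|---|
| Unpooled variance | 123 |
| Arcsine | 125 |
| Pooled | 126 |
| Pooled, continuity-corrected | 138 |
| One-sided | 99 |
| One-sided, continuity-corrected | 111 |

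None gives 150. Nor is 150 the number for another customary power: 85% needs 143 (156 corrected) and 90% needs 167 (180 corrected).

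Could the 10% loss already be inside the 150? The nearest route is 138 / 0.90 = 153.3. But step 1 shows that the loss is applied between 150 and 418, so this would count it twice.

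**3. Power at 150 per arm.** Power = Φ{[d·√n − 1.960·√(2p̄(1−p̄))] / √(p1(1−p1) + p2(1−p2))}, with √150 = 12.247.

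- 21% vs 37%: (0.16 × 12.247 − 1.2577) / 0.6317 = 0.7018 / 0.6317 = 1.111, so Φ = 86.7%
- 21% vs 34%: p̄ = 0.275, √0.39875 = 0.6315, × 1.960 = 1.2377, and √0.3903 = 0.6247. Then (0.13 × 12.247 − 1.2377) / 0.6247 = 0.3545 / 0.6247 = 0.567, so Φ = 71.5%

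| Treated rate (control 21%) | Pooled test | Continuity-corrected | Fisher's exact |
|---|---|---|---|
| 37% | 86.7% | 83.7% | 84.1% |
| 35.5% | 80.0% | – | – |
| 34% | 71.5% | 66.9% | 67.5% |

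A one-sided test at 37% gives 92.4%, further from 80%.

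**4. Number needed at the reported effect.** For 0.21 vs 0.34, n = (1.2377 + 0.842 × 0.6247)² / 0.0169 = 184.01, so **185 per arm** (200 with continuity correction). With the plan's own inflation, 185 / 0.40 / 0.90 = 514 randomised per arm, or 1,028 in total.

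**The case against.** The strongest reply has three parts.

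**The mismatch is on the safe side.** For 21% vs 37% the trial has more power than it claims, whichever two-sided test is used. Rounding up, or an allowance not described in a condensed article, could lie behind 150. This stands as to direction. It does not make the printed figures agree.

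**37% is a postulate.** The section does not say that 37% was observed, and the Background openly gives 34%. The article also contains reasons to plan higher: the larger difference when CPR began within 10 minutes, the exclusion of response times over 15 minutes, and the aim of earlier and less interrupted cooling (Discussion). This stands too. A target above 34% is not an error in itself. But the sample size paragraph gives none of these reasons, and it keeps the control rate at 21% while raising only the treated rate.

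**The earlier outcome may not be the same one.** The Background gives no time point for the 21% and 34%, whereas the present outcome is at 90 days. So 71% is a sensitivity figure, not the trial's true power.

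A reader might go further in three directions that the article does not support:

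- **That the DSMC will be misled, or that the 16-point effect drives futility stopping.** The article does not say who calculates conditional power or under which effect.
- **That the 40% ROSC rate contradicts the earlier trial.** Dividing overall survival by survival among those admitted gives 15/44 = 34% and 13/31 = 42%. These rest on rounded percentages and average 38%, close to 40%. Power for 37% would stay near 85%.
- **That 37% is absent from the earlier trial's results.** Only the Background's summary of that trial is at hand, so this cannot be said.

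**Conclusion.** The statement is wrong as written. On the article's own rates and alpha, 80% power needs 126 admitted patients per arm (138 corrected), and 150 per arm gives about 87% (about 84% with Fisher's test or continuity correction). No customary variant gives 80%.

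A reader might infer that the trial is underpowered for its own assumptions. It is not, because for 37% the discrepancy is conservative. The weakness is the unexplained 3-point step above the result reported for the trial named as the source. At 21% vs 34%, power is about 71% (Fisher about 67%). The effect that 150 per arm does detect with 80% power, 21% vs 35.5%, is neither the postulated nor the reported one.

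This rests on a two-sided test at 0.05, 150 evaluable admitted patients in each arm, a control rate of 21%, and a negligible effect of the interim boundary (p ≤ 0.001) on final power.

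**What to change.** Keep 836 patients and restate the calculation:

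- Name the test and say that it is two-sided, if it is.
- State that 150 evaluable admitted patients per arm give about 87% power for 21% vs 37%, 80% for 21% vs 35.5%, and about 71% for the 21% vs 34% reported in the Background. These are pooled-test figures. If Fisher's test or a continuity correction is to be used, give about 84% at 37% and about 67% at 34%.
- Say that 37% is a target above the earlier trial's overall result, and give the reason for it.

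This changes wording only and adds no patients. The downside is that the stated power at the previously observed effect becomes less favourable.

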## Methods/design

### Study design

This is a prospective, multi-centre, randomized, single-blind, controlled study conducted by the emergency responders of different emergency medical systems (EMS). In the treatment arm, patients will be immediately cooled by paramedics and/or emergency physicians using the RhinoChill device. Intra-arrest cooling will be continued after ROSC and until hospital admission for patients who will be resuscitated while it will be interrupted at the end of CPR in case of unsuccessful resuscitation. In the control arm, patients will receive standard of care and will be treated with TH after arrival at the hospital.

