### Study treatment

The resuscitation attempt will follow current guidelines [24] to the greatest extent possible. After airway management (i.e. laryngeal mask or intubation), patients are randomized to early cooling or standard care. In patients randomized to early cooling, the RhinoChill catheters should be placed and cooling initiated immediately. To place the nasal catheters and start cooling takes approximately 1 minute. Cooling should be performed with the oxygen flow set to 40 L/min. There should be no changes to the care received by patients randomized to the control arm. Resuscitation attempts should be continued for at least 30 minutes after EMS arrive on the scene in all patients before deciding that further interventions are futile.

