### Post-resuscitation care

Return of spontaneous circulation will be defined as obtaining an organized rhythm and palpable pulse sustained for 20 minutes. Once an organized rhythm and palpable pulse is achieved, subjects will have their temperature taken via the tympanic route, stabilized and then be transported to the hospital. If a patient wakes up after ROSC is achieved, cooling will be discontinued; on the opposite, subjects will, if needed be intravenously administered bolus doses of sedation and analgesia for transport to the hospital. Doses of sedation and analgesia will be dictated by the institutional standard cooling protocol. The oxygen supply in the transport vehicle should be used to continue RhinoChill cooling during transport to the hospital. Normal transport procedures will be used for patients randomized to the control arm. Infusions of cold saline or cooling with cold packs will not be permitted in the pre-hospital setting for either group. Upon hospital arrival, a systemic temperature probe will be placed (i.e., bladder, arterial, rectal) and core temperature will be recorded. Systemic hypothermia on arrival at Intensive Care Unit (ICU) for both patient groups (treatment and control) will be performed as follows:

–Duration of hypothermia for at least 24 hours.

–Target temperature 33°C ± 1°C.

–Recording of core- and tympanic temperature every 15 minute during the induction period (i.e., until target temperature is reached).

–Rewarming rate at 0.2-0.5°C / hour.

–Control of post-cooling hyperthermia.

Subjects randomized to the early cooling group with the RhinoChill shall continue being cooled with the RhinoChill until systemic cooling procedures can be started. Intravenous sedation, analgesia and neuromuscular blockade (if used) should be initiated upon hospital arrival according to institutional cooling protocols. Doses should be adjusted as necessary over the course of cooling/re-warming. After the subject has been prepared with the standard hypothermia device, the RhinoChill should be turned off, but the intranasal catheters should be left in place while transitioning the subject to the standard hypothermia protocol.

Intermittent activation of the RhinoChill may be considered if the core temperature does not continue to drop via the systemic cooling method. Cooling via the RhinoChill system will be halted immediately if any adverse event related to the use of the RhinoChill develops.

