For those patients in the control group, the standard cooling procedure will be started as soon as practical. Intravenous sedation, analgesia and neuromuscular blockade (if used) should be initiated upon hospital arrival according to institutional cooling protocols. Doses should be adjusted as necessary over the course of cooling/re-warming. Temperatures (tympanic and core) will be monitored periodically over the first 48 hours after hospital arrival for all patients. ECG, peripheral oxygen saturation, heart rate and blood pressure monitoring will continue throughout the acute care period. Ventilation settings should be adjusted to maintain arterial oxygen saturation 94-98% (e.g., PaO2 80–120 mmHg) and normocapnia (e.g., PaCO2 35-45 mmHg). A positive end-expiratory pressure (PEEP) level should be adjusted to reduce FiO2 below 60%, whenever possible. Electrolytes will be substituted as necessary to maintain normal ranges. Blood pressure should be kept above 65 mmHg at all times. Drops in pressure should be treated primarily with crystalloid fluids. If sufficient pressure control cannot be achieved with fluids alone, vasopressor drugs, such as adrenaline or norepinephrine, should be used. Serum blood glucose should be kept between 110 and 150 mg/dl with insulin administration. Enteral feeding will be initiated according to local guidelines.

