### Data collection

Data collection concerning the cardiac arrest will include time to collapse; bystander CPR; location; time of arrival of basic and advanced life support, ALS, teams; time of emergency call; time of first emergency medical team initiated CPR, patient characteristics (i.e. gender, weight, age, comorbidities), resuscitation effort (time CPR is initiated by the first emergency medical staff, EMS, responder; time cooling initiated - if cooled; mechanical CPR, if not manual; time intravenous access obtained; first rhythm; total adrenaline/epinephrine dose; shock time, strength, and success; additional medication(s) and dose(s); time airway is secured; recurrent VF or re-arrest; time randomized; time ROSC or death declared). Also, quality of CPR, including the number and depth of chest compressions/min as well as CPR hands-off time, will be recorded whenever possible. After hospital admission, tympanic temperature; heart rate, peripheral oxygen saturation (SpO2), mean arterial pressure, end-tidal carbon dioxide (EtCO2), arterial blood gas analysis, initial ECG findings and Glasgow coma score will be recorded. Concomitant interventions (e.g., coronary angiogram, aortic balloon pump, bypass surgery, internal cardiac defibrillator placement) will also be recorded. The systemic cooling procedures, including the system used, the core temperature location, the duration and the hypothermia reversal algorithm will be recorded.

The Steering Committee has the responsibility to perform periodic and spot checks visits to monitor the progress of the clinical study. Completed Case Report Forms (CRFs) will be reviewed for completeness, compliance with the investigation plan, and appropriate device use and accountability. Case Report Forms will be provided to each site for each subject enrolled in the study. Required data concerning patient treatment and test results will be recorded on the CRFs at the time of the procedure or as soon as possible thereafter. Information recorded in the CRFs will be corroborated by data in the subject’s medical records. Completed and monitored CRFs will be uploaded on a website developed by the PI, which will be overseeing data entry and data quality management. Data on safety will be provided to the Steering Committee with regular time intervals.

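### The subgroup defined by cooling started within 15 minutes can in practice be met only in the trans-nasal cooling arm, so as worded it has no randomised comparator

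*Protocol article*

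**What the plan says.** The Statistical analysis section names two timing subgroups in one sentence. The first takes patients whose first EMS CPR came early, with a 10-minute limit. The second takes those "or where cooling was started within 15 minutes". No comparison group is given for the second.

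Other sections fix when cooling can start in each arm:

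- **TNEC arm** (Study treatment): randomisation follows airway management, and then "In patients randomized to early cooling, the RhinoChill catheters should be placed and cooling initiated immediately". Placing the catheters and starting the device is put at about 1 minute.
- **Control arm** (Study design): "In the control arm, patients will receive standard of care and will be treated with TH after arrival at the hospital".
- **Both arms before hospital** (Post-resuscitation care): "Infusions of cold saline or cooling with cold packs will not be permitted in the pre-hospital setting for either group".
- **Controls in hospital** (same section): "For those patients in the control group, the standard cooling procedure will be started as soon as practical".

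Under Data collection, the resuscitation record holds "time cooling initiated - if cooled". The same list includes the time of the emergency call and the time of randomisation, with no restriction by arm. The Statistical analysis section states an intention-to-treat basis.

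**The concern.** A subgroup analysis in a randomised trial keeps its protection against confounding only if membership is decided in the same way in both arms, by something that allocation cannot influence. Start of cooling is the treatment itself. It happens after randomisation, and in the field it happens in one arm only.

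Patients who are cooled quickly tend to be those whom the crew reached quickly, whose airway was secured quickly and whose scene allowed it. These features plausibly carry a better prognosis whatever the device does. The protocol itself treats response time as important: it excludes patients whose interval from call to first EMS CPR exceeds 15 minutes, and its Background relies on a time-to-CPR subgroup of the previous trial.

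At stake is the reading of one pre-specified subgroup. Earlier cooling is the idea that the trial tests, and pre-specification would lend this analysis a credibility that its definition cannot support.

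**Working it through.** The documents give no effect, sample size or power for this subgroup, so there is no stated figure to reproduce. The check is first one of logic, then an illustration.

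**1. Who can meet the condition?**

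| | TNEC arm | Control arm |
|---|---|---|
| Cooling before hospital | Yes, straight after randomisation | No; treated in hospital, with cold saline and cold packs barred on the way |
| Patients who die at the scene | May have been cooled | Never cooled |
| Cooling started within 15 minutes of collapse, call, EMS arrival or randomisation | Possible | Essentially impossible |

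Only a clock that started at hospital arrival could admit controls. That does not fit a condition paired with first EMS CPR within 10 minutes.

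**2. Which contrasts does the wording leave?** Early-cooled TNEC patients can be set against all controls (selected against unselected) or against later-cooled TNEC patients (not randomised).

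**3. Direction and size if the device does nothing.** Let a share *p* of patients be fast, with outcome rate *f*, and the rest slow, with rate *s*.

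- Against all controls: *f* − [*p f* + (1 − *p*) *s*] = (1 − *p*)(*f* − *s*). With *p* = 0.5 this is half the gap.
- Against later-cooled TNEC patients: *f* − *s*, the whole gap.

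The rates below are assumed and come from no part of the documents; *p* = 0.5 throughout.

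| Fast / slow | Spurious difference against all controls | Against later-cooled TNEC |
|---|---|---|
| 25% / 20% | 0.25 − 0.225 = 2.5 points | 5 points |
| 30% / 15% | 0.30 − 0.225 = 7.5 points | 15 points |
| 35% / 10% | 0.35 − 0.225 = 12.5 points | 25 points |

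**4. Simulation with no treatment effect.** Assumed inputs: log-normal time to randomisation (sigma 0.35) with median 15, 18 or 22 minutes; placement 1 to 3 minutes; odds ratio for good outcome per minute of delay 1.00, 0.95 or 0.90. The average outcome rate was set to the protocol's 21%. There were 2,000,000 simulated patients per scenario. Entries are early-cooled TNEC minus all controls, in percentage points.

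| Median time | OR 1.00 | OR 0.95 | OR 0.90 |
|---|---|---|---|
| 15 min | +0.1 | +4.6 | +9.0 |
| 18 min | −0.1 | +7.0 | +14.5 |
| 22 min | +0.2 | +11.1 | +22.6 |

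The artefact vanishes if delay has no bearing on outcome and otherwise favours TNEC. When the subgroup was instead defined in both arms by time to randomisation (13 minutes or less), the difference lay between −0.1 and +0.4 points in all nine scenarios, which is simulation noise.

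**The case against.** The strongest reply is that the article never says early-cooled TNEC patients will be compared with all controls. A within-arm description would be legitimate. So would a time-matched analysis, with controls taken by their time of randomisation, and the unseen analysis plan could specify either. This stands as far as it goes: the biased contrast is not inevitable, and a reader who infers that the trial has committed itself to it goes beyond the text. It does not rescue the wording, which fixes membership by start of cooling, and no other section supplies a counterpart for controls.

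A reader might also infer that the illustrations measure the bias and set them against the 16-point effect in the sample-size paragraph (21% to 37%). The documents do not support that. The fast/slow rates, the half-and-half split, the delay distribution and the odds ratios are all assumed. The 15-minute limit on call to first EMS CPR narrows one source of prognostic spread. The 16 points refer to admitted patients, whereas the illustrations are not tied to any analysis population.

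Three further limits hold:

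- The unstated start of the 15-minute clock is detail that a condensed article may leave to the full protocol, so it is not held against the plan.
- The definition of return of circulation as a pulse sustained for 20 minutes adds nothing here, since it defines an outcome and is not stated as a condition for starting hospital cooling.
- The timing question also has a sound subgroup in the same sentence, EMS CPR within 10 minutes, which is defined alike in both arms.

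**Conclusion.** The point holds for the definition as written: one arm cannot in practice meet it, so the subgroup has no randomised comparator, and the obvious substitutes mix the device effect with speed and ease of access. This is a stated rule that does not work, not a missing detail.

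The direction of bias favours TNEC, on the assumption that longer delay worsens prognosis. The size is not established; it could be anywhere from nothing to large, depending on inputs that the documents do not give.

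A reader might take this as a threat to the trial's conclusion. It is not: the primary and secondary endpoints, the sample size, the interim rules, the rhythm strata and the 10-minute CPR subgroup do not depend on this clause. It should be fixed, at the rank of a subgroup definition.

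**What to change.** Replace the clause with a subgroup defined identically in both arms: interval from emergency call to randomisation, at or below versus above one cut-off stated in advance. Test it as a treatment-by-interval interaction rather than by separate within-subgroup tests. Whatever set of patients is analysed, both arms are then selected by the same rule. Report actual time to cooling in the TNEC arm descriptively only, labelled as non-randomised.

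The cost is one sentence in the protocol or analysis plan and no new data, because both times are already listed under Data collection. The downside is that time to randomisation stands in for time to cooling. It is a close proxy, since cooling is to follow randomisation immediately and placement takes about 1 minute, but it will not capture individual delays in placement.
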